### Study Treatments

The intervention consisted of consumption of five lozenges daily. We chose lozenges as the delivery method on the basis of a report that lozenges were strongly preferred to gum in a sample of veterans [8] and our own perception that gum would be objectionable to some proportion of potential participants.

Each active lozenge contained 1.0 g of xylitol as a sweetening agent. The placebo lozenge was identical in size and color to the active lozenge but was sweetened with sucralose, which lacks any plausible biologic anti-caries properties. Both the active and placebo lozenges were peppermint flavored. The lozenge used for the run-in period was also sweetened with sucralose, but was spearmint flavored to avoid inadvertent unblinding of participants.

The available literature suggests, but does not demonstrate conclusively, a possible threshold of caries prevention effectiveness around 3 exposures each day with a total daily intake of 3-4 g [9]. Because we were unable to identify a manufacturer capable of compounding both active lozenges containing more than 1 g of xylitol and indistinguishable placebo lozenges, our choice of a 5 lozenge/day regimen represents a compromise between increased assurance of achieving a therapeutic dose and practicality.

Since xylitol has the capacity to act as a laxative in some individuals, participants were asked to gradually increase the number of lozenges they took each day from 1 to 5 during the first 10 days. This "ramping up" was done both during the run-in period and at the initiation of the intervention post randomization.

Lozenges were supplied to participants in containers of 75, with the participant's ID number permanently marked on the container. Seven containers constituted a 3-month supply with some extra lozenges. Participants also received a pocket container capable of holding a day's supply of five lozenges. The active and placebo lozenges were prepared in separate manufacturing runs, and samples of each run were assayed to confirm the xylitol content. The lozenge used during the run-in period was also prepared in a separate run, but was not assayed.

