### Study Outcomes

#### Primary Outcome Variable

The primary study outcome is the cumulative D_2 _or Filled Surface (D_2 _FS) increment (root and coronal surfaces combined) cumulated from baseline through the three follow-up examinations. Use of the cumulative, combined D_2 _FS increment measure allows comparison with existing literature and increases confidence that any effect detected represents the prevention cavitation, which has substantial clinical implications for individuals who experience it.

The D_2 _FS increment is computed as the weighted sum, across tooth surfaces, of changes in surface status associated with 64 pre-defined transitions in tooth-surface integrity (Table 1). Our weighting scheme assigned a range of -1, 0, or +1, with transitions to a worse status receiving positive weights and transitions (reversals) to a better status receiving negative weights. No reversals are considered valid for the D_2_FS increment. A transition that reflects no change (e.g., F to F), a change from D_2 _to treated status (F or C), or to or from an unscorable status (Y or M) is scored 0 and hence effectively excluded from analysis. A transition from sound (S) to crowned (C) is given a score of 0 to minimize the influence of non-caries-related treatment on increment counts. Transition from S to CD_2 _is considered implausible given annual examinations. After completion of bootstrapping analyses of a caries increment dataset from another study, we concluded that the optimal way to handle unlikely or implausible transitions is to ignore them (i.e., assign a weight of zero). Hence for our primary analysis the bolded cells in Table 1 will be ignored, although they will be included in an outcome in planned secondary analyses.

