#### Other Study Measures

In addition to the caries examination data, other study data are collected periodically to assist in monitoring participant safety and as measures of risk factors and other mediators of caries incidence. Additional data collected at baseline describe participants' demographic characteristics, self-reported oral hygiene behaviors, fluoride exposure, and exposure to antibiotics. Adherence is measured by self- reported lozenge use at each visit and by the cumulative bottles of lozenges used during the study. Staff also query participants as to receipt of preventive dental care and use of over-the-counter preventive agents since the last contact. Forms used for all data collection are available on the study's public website at http://www.xactstudy.org.

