### Analysis

#### Missing Data

We expect to have complete data on baseline measures, so missing data are likely to arise only with respect to the annual and final examination visits. Since our analysis approach accounts for time at risk, the primary outcome of combined D_2_FS increment will be imputed from baseline to year 1 only for participants who failed to return for any annual visits, and the time-at-risk will be defined as the target date for the first annual visit. We will use an inclusive model to improve the likelihood of unbiased imputed values [17]. We will multiply impute missing data using data augmentation with Markov Chain Monte Carlo sampling. Five to eight versions of the final analysis dataset will be created and analyzed using identical procedure, followed by combining the results so that variation between imputation versions is incorporated in the standard error and p-value.

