#### Primary Outcome Analysis

The primary analyses will be an intent-to-treat (ITT) analysis, on a sample that includes all randomized patients and classifies them according to their assigned treatment group, regardless of their adherence to the protocol. The primary outcome will be analyzed in a negative binomial regression model (using SAS^® ^PROC GENMOD) in which treatment group and clinical center indicators are included as fixed categorical design factors. Planned (*a priori*) covariates are age and age-squared, intensity of preventive regimen, oral hygiene behavior measures, and severity of baseline caries, which is defined as the sum of decayed surfaces at the baseline examination. We will include the natural log of person-years at risk, ln(*t *_i_), as an offset to adjust for length of time since the participant was randomized. Formally, the model is,

ln(μi)=β0 +  Tiβ1+ S1β2 + S2β3 + ci'γ + ln(ti),

or equivalently,

ln(μi/ti) = β0 + Tiβ1 + S1β2 + S2β3++ ci'γ,

where *μ *is the mean observed increment, *μ */t is the incidence of new progressions per year, T is the treatment indicator (0 = placebo, 1 = xylitol), S_1_, S_2 _are clinical site indicators, **c**_i _represents a vector of covariates, and **β **and **γ **represent vectors of parameters to be estimated. The resulting *β*_1 _coefficient thus has the interpretation of the ln(relative risk) for progression for the xylitol compared to placebo lozenges, and the null hypothesis test of no difference between treatment arms is a test of H_0_: *β*_1 _= 0 vs. the alternative hypothesis H_1_: *β*_1 _< 0. The actual fraction of a year's exposure to the lozenges will be used where known, otherwise, the offset will be set to the midpoint of the period between the first examination missed and the last examination attended. In secondary analyses of the primary outcome, we will conduct sensitivity analyses by applying the alternative distributional models (Poisson, mixture models) mentioned above to the same data.

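### The primary model's offset has two incompatible definitions, time since randomization and time on lozenges; the second, followed literally, breaks the intent-to-treat analysis

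*Protocol article*

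**What the plan says.** All references are to the protocol article.

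- **Primary Outcome Analysis, before the model.** ln(t_i), the log of person-years at risk, is included "as an offset to adjust for length of time since the participant was randomized".
- **Primary Outcome Analysis, after the model.** The rule for the value to enter is "The actual fraction of a year's exposure to the lozenges will be used where known". A fallback covers participants for whom that value is not available: "otherwise, the offset will be set to the midpoint of the period between the first examination missed and the last examination attended".
- **Primary Outcome Analysis, opening.** The analysis is intent-to-treat, with participants classified by assigned arm "regardless of their adherence to the protocol".
- **Primary Outcome Variable.** The increment is "cumulated from baseline through the three follow-up examinations". Nothing restricts it to time on lozenges.
- **Missing Data.** For participants who attend no annual visit, a year-1 increment is imputed and "the time-at-risk will be defined as the target date for the first annual visit".
- **Other Study Measures.** Adherence is recorded by self-report and "by the cumulative bottles of lozenges used during the study".

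**The concern.** The offset is the denominator of the primary rate, so it must cover the same interval as the count above it. The count runs from baseline to the examinations. Time since randomization matches that interval, and time on lozenges does not.

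With lozenge time in the denominator, lesions that appear after a participant stops still count while the time in which they appeared does not. Stopping happens after randomization and may depend on the arm. The Study Treatments section itself gives a possible reason: "Since xylitol has the capacity to act as a laxative in some individuals". A difference in stopping could then move the rate ratio when xylitol does nothing, or hide or exaggerate a real benefit.

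The words "The actual fraction of a year's exposure to the lozenges will be used where known" could apply to most participants, because lozenge use is asked about every quarter and bottles are counted.

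**Working it through.** **1. The plan's own figure.** The article gives no figure for the offset. Its sample size supplies the planning inputs used below: placebo increment 3.7 over three years, overdispersion 3.0, 20% reduction, one-sided alpha 0.025, power 80%. For Poisson regression with a binary covariate split evenly,

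N = 3.0 × (1.96 × √4 + 0.842 × √4.5)² / (3.7 × (ln 0.8)²) = 530.

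Dividing by 0.70 (10% attrition per year, summed) gives 757, close to the stated 750. Lozenge exposure plays no part, so correcting the offset leaves the target unchanged.

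**2. One participant.** The final examination is at 33 months, or 2.75 years. Stopping at 0.5 year multiplies the rate by 2.75 / 0.5 = 5.5. Stopping at 1 year multiplies it by 2.75.

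**3. Rate ratio by hand, no true effect.** Assume that stopping times are uniform on 0.25 to 1.5 years (mean 0.875; mean of 1/s = ln 6 / 1.25 = 1.433) and that all stoppers are examined to 2.75 years. Stopping is 20% on xylitol and 10% on placebo. For a given dispersion, negative binomial regression weights each person's rate between two extremes:

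- Weight proportional to time (pooled rates): mean denominators are 0.9 × 2.75 + 0.1 × 0.875 = 2.5625 (placebo) and 0.8 × 2.75 + 0.2 × 0.875 = 2.375 (xylitol). Rate ratio 2.5625 / 2.375 = 1.08.
- Equal weights (mean of individual rates): mean inflation is 0.9 + 0.1 × 2.75 × 1.433 = 1.294 (placebo) and 0.8 + 0.2 × 2.75 × 1.433 = 1.588 (xylitol). Rate ratio 1.588 / 1.294 = 1.23.

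The model's answer should lie between 1.08 and 1.23. Simulation gives about 1.15.

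**4. Simulation.** N = 691, yearly rate 3.7/3, variance-to-mean ratio 3, follow-up 2.75 years, stopping times as in step 3, all stoppers examined to the end, 2,000 replicates, Wald test at one-sided 0.025. Each cell gives the rate ratio, then the probability of rejecting in favour of xylitol.

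| Stopping, xylitol / placebo | True ratio on lozenges | Offset: time since randomization | Offset: time on lozenges |
|---|---|---|---|
| 20% / 20% | 1.00 | 1.00, 0.025 | 1.00, 0.044 |
| 25% / 20% | 1.00 | 1.00, 0.025 | 1.08, 0.008 |
| 30% / 20% | 1.00 | 1.00, 0.025 | 1.17, 0.001 |
| 20% / 25% | 1.00 | 1.00, 0.025 | 0.93, 0.176 |
| 20% / 30% | 1.00 | 1.00, 0.025 | 0.86, 0.411 |
| 20% / 20% | 0.80 | 0.83, 0.74 | 0.84, 0.53 |
| 30% / 20% | 0.80 | 0.84, 0.67 | 1.00, 0.04 |
| 20% / 30% | 0.80 | 0.83, 0.74 | 0.72, 0.91 |

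The values 0.83 and 0.84 under time since randomization are the expected intent-to-treat dilution from stopping. In repeated runs of the equal-stopping case with true ratio 0.80, power was 0.74 to 0.79 with time since randomization and 0.50 to 0.55 with time on lozenges.

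**5. If stoppers also leave follow-up.** Stopping 20% (xylitol) against 10% (placebo), no true effect:

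| Share of stoppers who leave | Rate ratio, lozenge offset |
|---|---|
| None | about 1.15 |
| Half | 1.07 to 1.10, depending on which examination is their last and which offset they receive |
| 80% | about 1.02 |

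**6. The midpoint fallback.** A participant last examined at 12 months who misses the 24-month visit would get t = 18 months, although lesions were counted only to month 12. The rate is multiplied by 12/18 = 0.67. For a participant who never returns, taking baseline as the last examination attended, the midpoint is 6 months, while the Missing Data section sets 12.

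**The case against.** The strongest reply is that follow-up time was meant throughout. The formal definition refers to randomization, and the Missing Data section speaks of time at risk and ties it to a visit date. The midpoint fallback also makes sense only for people who left follow-up, since someone who attends every examination has no first missed one. On this view the sentence is a dropout rule that uses exposure loosely, and the participant who stops early but attends to 33 months is not its target.

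That reading is plausible, and it limits the point. A reader might infer that the trial will in fact use lozenge time and that its primary estimate is therefore biased. The article does not support so firm a statement. It does name exposure to the lozenges, however, and a programmer following it would code that. If follow-up time was meant, the sentence is still wrong and needs the same correction.

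Two further replies carry weight:

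- Large bias needs stopping to differ by arm, and the article reports no stopping rates. The laxative remark gives a reason, not evidence, and the gradual increase over the first 10 days responds to it. The run-in does not remove the possibility, because its lozenge contained sucralose and so could not screen out intolerance of xylitol.
- Rates are inflated only for stoppers who keep attending. Step 5 shows how quickly the effect shrinks as more of them leave.

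That a separate analysis plan might settle the matter is no answer. The article does not leave the offset open; it states a rule that conflicts with its own definition.

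**Conclusion.** The point stands as an inconsistency that is wrong as written: the primary model's offset has two definitions that cannot both be used. The lozenge-exposure rule conflicts with the intent-to-treat statement and with the interval over which the increment is counted.

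The consequences are conditional on the literal reading:

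- **Stopping differs by arm.** The rate ratio is biased. With 20% (xylitol) against 10% (placebo) and no effect, it is about 1.15 if all stoppers stay and 1.07 to 1.10 if half leave. More stopping on placebo reverses the direction, so a reader should not infer that the bias always works against xylitol.
- **Stopping is equal.** The ratio is essentially unbiased. At 20% in both arms, power falls from about 0.75 to 0.79 to about 0.5, and one-sided error is about 0.044 instead of 0.025.

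The contradiction is certain from the text. The sizes are not: they rest on assumed stopping shares, stopping times and attendance after stopping.

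**What to change.** 1. Define t_i once, as time from randomization to the last caries examination attended, regardless of lozenge use. This is the interval over which the increment is counted.
2. For participants with no follow-up examination, where that definition would give t = 0 and an undefined logarithm, keep the Missing Data rule: an imputed year-1 increment with the first annual visit's target date as time at risk.
3. Delete the lozenge-exposure wording and the midpoint fallback. The fallback adds time in which no increment could be counted and conflicts with the Missing Data section.
4. Use lozenge exposure only in a secondary adherence analysis, labelled as such.

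The cost is a short rewrite of the offset text, a cross-reference to Missing Data and a small change to the code. Follow-up time comes from the randomization and examination dates, so no new data are needed.

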### Study Schedule

Figure 1 summarizes the trial flow from a participant's perspective. The study requires a participant to visit the clinic a minimum of 5 times. Screening was followed as soon as possible by an enrollment visit. The enrollment visit is followed by a placebo run-in period. Adherent, eligible enrollees were randomized at the baseline visit. Participants are then scheduled to return at 12 months, 24 months and 36 months for caries examinations, with quarterly telephone contacts between examination visits. Before the 24-month visits began, the final examination schedule was shifted to 33 months, to adjust for slower than expected completion of enrollment.

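### The midpoint fallback for the offset runs person-time half an interval past the last examination at which a lesion could be counted, which biases the rate ratio towards whichever arm loses more participants after a follow-up examination

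*Protocol article*

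**What the plan says.** All of this is in the Protocol article.

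- **Count.** Under Primary Outcome Variable, the D2FS increment is "cumulated from baseline through the three follow-up examinations". A new lesion or filling enters the count only when an examiner records it at a visit.
- **Imputation.** Under Missing Data, the increment is imputed "only for participants who failed to return for any annual visits", from baseline to year 1, and for them "the time-at-risk will be defined as the target date for the first annual visit".
- **Offset.** Under Primary Outcome Analysis, ln(person-years at risk) enters "as an offset to adjust for length of time since the participant was randomized". The rule for filling it in has two parts. The preferred value is the participant's own time on treatment: "exposure to the lozenges will be used where known". When that time cannot be established, the plan falls back on a date between two visits: "otherwise, the offset will be set to the midpoint of the period between the first examination missed and the last examination attended".
- **Visits.** Under Study Schedule, participants "return at 12 months, 24 months and 36 months for caries examinations"; later "the final examination schedule was shifted to 33 months".

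**The concern.** In a rate model with an offset, the person-time must cover the period over which the events could be counted. For a participant lost after the 12- or 24-month examination, that period ends at the examination. The midpoint is a fair guess at when the participant left the study, but nobody examined the teeth between the last visit and that date. Half an interval enters the denominator with no chance of an event in the numerator, so the quantity that the model calls incidence per year is too low for these participants.

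The offset also carries weight here. The Missing Data section restricts imputation to participants with no annual visit on the ground that the analysis accounts for time at risk, so for everyone else lost to follow-up the offset is the handling of missing data. The planned sensitivity analyses change the distribution and reuse the same data, so they would carry the same offset and would not show the problem. At stake are the treatment rate ratio and its one-sided test whenever the arms differ in loss after a follow-up examination.

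**Working it through.** **The plan's own figure.** The Sample Size section gives 750 in total: 20% reduction, 80% power, one-sided alpha 0.025, overdispersion 3.0, attrition 10% per year. Assuming 1:1 allocation and the central placebo increment of 3.7, the Poisson-regression formula N = 3.0 × (1.96 × √4 + 0.84 × √(2 + 2/0.8))² / (3.7 × (ln 0.8)²) gives 531 evaluable, and 531/0.70 is about 759. A Wald form gives 576, and 576 × 1.3 is about 749. The target is reproduced to within 3%, although the article does not say which placebo value or inflation produced it. It does not depend on the offset rule.

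**Per participant (time covered by the count / time in the offset).**
- Last seen at 12 months, 24-month visit missed: 12/18 = 0.667, so 33% too low.
- Last seen at 24 months, 33-month visit missed: 24/28.5 = 0.842, so 16% too low. With a 36-month final visit, 24/30 = 0.80.
- No follow-up examination: imputed one-year count over 12 months, ratio 1.00.
- All visits attended: ratio 1.00, taking person-time to the 33-month visit.

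**Per arm.** With yearly loss d and a constant caries rate, the fractions lost before the 12-month visit, before the 24-month visit, before the final visit and never are d, d(1−d), d(1−d)² and (1−d)³. Their counts cover 1, 1, 2 and 2.75 years; their offsets are 1, 1.5, 2.375 and 2.75 years. At the plan's 10% in both arms, the totals are 2.357 counted years over 2.432 offset years = 0.969. At an assumed 15% they are 2.183/2.288 = 0.954.

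The design standard error of the log rate ratio is |ln 0.8|/(1.96 + 0.84) = 0.080. The one-sided error below is 1 − Φ(1.96 + ln(null ratio)/0.080). Every split by arm is an assumption.

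| Yearly loss, xylitol / placebo | Factor, xylitol | Factor, placebo | Null ratio | True 0.80 appears as | One-sided error |
|---|---|---|---|---|---|
| 10% / 10% | 0.969 | 0.969 | 1.000 | 0.800 | 2.5% |
| 12% / 8% | 0.963 | 0.975 | 0.988 | 0.790 | 3.6% |
| 15% / 5% | 0.954 | 0.984 | 0.970 | 0.776 | 5.8% |
| 8% / 12% | 0.975 | 0.963 | 1.012 | 0.810 | 1.7% |
| 5% / 15% | 0.984 | 0.954 | 1.031 | 0.825 | about 1% |

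**Simulation of the offset negative binomial model.** Inputs: 691 participants, rate 3.7/3 per year, dispersion (3 − 1)/3.7 = 0.54 treated as known, no covariates, 3,000 null replicates and 800 at a ratio of 0.80.
- Loss 15% / 5%: null ratio 0.963, one-sided error 8.2%; a true 0.80 appears as 0.773.
- Loss 20% / 10%: null ratio 0.968, error 6.4%.
- Loss 5% / 15%: null ratio 1.038, error 1.1%; a true 0.80 appears as 0.834, with power 68% against 84% when person-time ends at the last examination.

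The fitted model thus shows a shift of up to about 4%, slightly more than the pooled rates. With person-time ended at the last examination, null ratios were about 1.00, the error was 2.5% to 3.2%, and a true 0.80 was estimated as 0.800 to 0.804.

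**Excess loss confined to year 1 (same pooled formula).** Xylitol 15%, 10%, 10% by year against placebo 10% each year: null ratio 1.0008. Xylitol 20%, 10%, 10% against 10%: 1.0016. Xylitol 15%, 5%, 5% against 5%: 1.0007. There is almost no bias, because these participants have matched count and time.

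**The case against.** Three objections have force.

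**Direction.** A reader might infer that the rule makes xylitol look better: the Study Treatments section notes a laxative effect, and the run-in used only sucralose lozenges. The documents do not support this. They give a single attrition figure and none by arm. The build-up to five lozenges takes place in the first 10 days, so dropout from intolerance would be expected early, before the 12-month examination, where the year-1 check shows almost no bias. If placebo loses more after an examination, the bias runs against xylitol. This objection stands in full.

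**Fallback only.** The midpoint applies only where lozenge exposure is not known, and quarterly calls and bottle counts may often supply it. If half of the affected dropouts had correctly matched person-time (an assumption), loss of 12% / 8% would give a null ratio of 0.994 and an error of 3.0%, and loss of 15% / 5% would give 0.985 and 3.9%. So the tabulated figures are upper values for this clause. The exposure clause does not cure the mismatch, though: time on lozenges need not end at the last examination either. Someone who stops the lozenges but keeps attending would get an offset that is too short and a rate that is too high.

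**Participants with no annual visit.** A reader might also infer that the two analysis sections contradict each other, because the midpoint between baseline and the 12-month visit is 6 months while Missing Data gives these participants about 12. Missing Data is the specific rule for this group and is naturally read as governing. This is at most a wording point.

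**Conclusion.** The mismatch between count and person-time is real and follows from the text alone. Where the midpoint is used, rates are understated by 33% for participants last seen at 12 months and by 16% for those last seen at 24 months with a 33-month final visit. Equal loss after a follow-up examination leaves the rate ratio unbiased and lowers both arms' rates by about 3% at 10% per year. Unequal loss biases the ratio in favour of the arm that loses more.

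The effect on the treatment comparison is modest and its direction cannot be told from the documents. It rests on assumed differences of 4 to 10 points per year that persist through follow-up, a constant caries rate, and use of the midpoint for every such dropout. A claim that the plan favours xylitol would go further than the documents allow. It is still worth correcting before analysis, since the one-sided error can more than double in one direction and power can fall appreciably in the other.

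**What to change.** Replace the sentence that sets the offset, covering both the lozenge-exposure clock and the midpoint fallback. For every participant with at least one follow-up examination, run person-years from randomization to the date of the last caries examination attended. For participants with no annual visit, keep the time at risk given under Missing Data, which matches their imputed one-year increment, and say that this rule governs them. Time on lozenges can still be used in an adherence analysis, but not as the denominator of the intention-to-treat rate.

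The cost is one sentence. It needs only the examination dates, which are already recorded, and it leaves the sample size and the rest of the model unchanged.
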